#### Questionnaire

The course participants are interviewed with a questionnaire concerning their level of knowledge, skills and safety in the care of trauma patients. These data are collected multiple times and reflect the participants’ subjective assessment of learning success in knowledge, skills and safety. A steady (metric) scale to ± 3 (positive/negative), including zero is used.

#### Data from the emergency department

In addition to actually study design, we will evaluate in a retrospective analysis the emergency department data. The investigation is and will be integrated regarding to detailed question and basic circumstances (e.g. ethics application, data privacy). Outcome measurement methods are developed.

#### Bias

In the before-after comparison, the participants know the approach to the patient through other training as well as that taught by the PHTLS. Even reading the PHTLS manual to prepare for the course might influence the participants, as would the fact that with each additional course, knowledge is disseminated by colleagues.

The cohorts of participants are paramedics. Typically, a German EMS crew does not treat seriously injured patients alone because paramedics are supported by emergency physicians in the field. Specific types of invasive skills and analgesia must be excluded from the cases because they are not performed by paramedics in the analyzed area.

##### 

**Mimes** For the baseline scenario, a participant performs the role of the patient; for the case studies, an instructed mime performs a standardized role of the patient. The quality of the representation and the accurate reproduction of specified symptoms might differ under those conditions.

##### Instructors

The vital signs and the non-presentable values are specified by the instructors. Each scenario could be defined differently or be variably stressed. Typically, the scenarios last approximately 10 minutes and are led by the instructors, and the team communication might be limited.

##### 

**Participants** The participants begin the course with different levels of motivation. They should have the identical theoretical knowledge level because they have read the PHTLS manual by the start of the course.

A type of Hawthorne effect may be caused by the fact that the participants know that they are being observed and might be filmed. Regarding the video recording, it is assumed that the more motivated participants offer to be the first team for the scenarios. If the identical participants are also used for the second video recording, the result might not be the result for the study cohort.

##### 

**Technical and organizational aspects** It is possible that the participants did not provide their consent to the recording. Technical problems could affect the video recordings. Organizational difficulties with the equipment (including unpunctual delivery loss of volume) and organizational fault in the recordings (wrong scenario, a bad camera position) might be possible.

#### Timeline

There are three defined time points for the measurement (Figure 1), as follows:

**Figure 1 F1:**
[figure not shown]
**Project timepoints t0 - t2.** “Subjective Safety of Participants” and “Scenarios” with three time points. Documentation with two time points. “Data Emergency Department” in process of planning.

#### Timepoint t0

Immediately prior to the PHTLS course (pre-course), the participants are interviewed with the questionnaire about their personal judgment regarding their skills, knowledge and safety in the care of trauma patients.

Prior to the start of the training program, the participants in 3-person-team treat a trauma-patient in a standardized case-based scenario, which is recorded on video. Additionally we want to evaluate the emergency department data from 2012.

#### Timepoint t1

At the end of the course, the participants’ survey with the questionnaire and the video recording are repeated to verify the changes (post-course).

#### Timepoint t2

After one year, the participants of the course will be interviewed again with the questionnaire, and the results will be verified by the video recordings in standardized case-based scenarios in practice. Data from the emergency department will be from 2014.

### Number of participants

#### Questionnaire

The number of questionnaires is based on the number of participants. The questionnaires at t0 and t1 will be collected directly, and a 100% return rate is expected. The questionnaire at time t2 will be web-based or distributed via email.

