### Hypotheses

Using a novel assessment tool (2.4.1), the following hypotheses will be tested:

▪ The introduction of PHTLS leads to improved quality of the documentation of actual field operations.

▪ The introduction of PHTLS leads to structured patient care by the ABCDE scheme [35], with priority-based interventions in case-based scenario training.

▪ The introduction of PHTLS leads the participants to a subjectively better and safer application of the principles.

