### Data collection methods

#### Questionnaire

The questionnaires at t0 and t1 are distributed and collected during the courses. The survey at t2 (after one year) is conducted using the questionnaires in parallel with the video analysis.

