### Data management

The data collection, coding, routing and analysis are coordinated with the data protection officer of the University of Tuebingen and the University of Tuebingen Hospital. The participants will be informed about the study prior to the course, and their questions about it will be answered.

The declarations of consent from the participants for the video analysis are available; the consent declarations assure permission for the recording, analysis and storage of the study data. The number of participants will be registered as a negative figure.

For the questionnaires and time contact, t2 is a declaration of consent for the available participants. This declaration is separated from the questionnaires on site. The questionnaires are pseudonymized with a four-digit code to represent the relationship between the different times, not to establish a connection to the participants.

The analysis of the defined characteristics in the EMS-operation protocols is unrelated to the patient data (including the last name, first name and date of birth). Hessian EMS law § 17 permits the use of evaluation data in the context of quality assurance.

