## Discussion

The aim to evaluate the effect of the training or the effect of the program on the patient outcome is understandable, complex and difficult. This study attempts to evaluate the effect of the training on the participants’ behavior.

This is a single-center study and based on scenarios of the treatment given to patients by paramedics. There is interest in developing a multi-center assessment tool. Concrete efforts will be made after the completion of this study to apply the tool for evaluation of emergency physician-based teams including air rescue personnel.

We are aware that the video analysis is influenced by a variety of factors. In addition, the result of the scenario-based patient care is not to transfer 1:1 to the real patient care. To increase the comparability and consistency, a member of the research group will supervise the recordings or even leads them through. Time t0 records are parallel, and the scenarios are directed by leading instructors briefed on the key points and identical criteria to apply to all the cases. An identical situation occurs with t1, with the difference being that in t1, the cases are sequential instead of parallel.

Initially it was planned to visualize the individual measures on a timeline. However, the flow in the scenario is disturbed by the information from the instructors, for example vital signs or by questions from the participants, so it does not seem sensible to use the real-time analysis. In addition, a range of skills such as laying intravascular access or prepare infusions are not real performed.

The results of the questionnaire for the subjective assessment of the participants should be available without special bias, especially we expect a very high response rate. The evaluation of the EMS-protocols focuses on three items, which are trained in the course. But since the SAMPLE scheme is widely used, it remains to be seen how the degree of compliance prior to the course and a possible change is measurable.

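### The low-bias statement for the questionnaire rests on a return rate the plan supports only at t0 and t1, while the remote one-year survey has no expected return and is compared unpaired

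*Protocol article*

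**What the plan says.** The third hypothesis is that "The introduction of PHTLS leads the participants to a subjectively better and safer application of the principles". It names no time point. The questionnaire records the participants' "subjective assessment of learning success in knowledge, skills and safety" at t0 (before the course), t1 (end of the course) and t2 (one year later). On the response scale: "A steady (metric) scale to ± 3 (positive/negative), including zero is used".

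On return, Number of participants (Questionnaire) says: "The questionnaires at t0 and t1 will be collected directly, and a 100% return rate is expected". The next sentence is "The questionnaire at time t2 will be web-based or distributed via email", with no return rate for t2.

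The t2 route is described in two other places. Data collection methods (Questionnaire) says: "The survey at t2 (after one year) is conducted using the questionnaires in parallel with the video analysis". Timepoint t2 speaks of a further interview using the questionnaire. Data management adds: "For the questionnaires and time contact, t2 is a declaration of consent for the available participants".

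Statistical methods matches the records by pseudonymous code, then specifies a two-sided t-test for unpaired samples at α = 0.05 across the three time points. The Discussion says the questionnaire results "should be available without special bias, especially we expect a very high response rate". The Bias section covers prior knowledge, mimes, instructors, motivation, awareness of being observed, and technical problems. It does not mention non-response at t2.

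**The concern.** The Discussion gives one reason for expecting little bias, a very high response rate, and applies it to the questionnaire as a whole. The plan backs that rate only where sheets are handed out and collected during the course. A year later the survey is remote, and Recruitment makes study participation voluntary although the course itself is required. Return at t2 is the part most exposed to loss, and it is the part with no expected figure.

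The choice of test adds to this. An unpaired comparison takes whoever has a value at each time point. With near-complete t0 data and partial t2 data, the two groups differ in composition as well as in time, so selective response could pass as a lasting gain or hide one. If the mode also changes from on-site forms to web or email at t2, that change coincides with the time contrast.

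**Working it through.** No questionnaire sample size, power or t2 return rate is stated, so there is no figure of the plan's own to reproduce. The 400 EMS operation protocols belong to the documentation hypothesis. The check asks how far t2 non-response could move the result.

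**Inputs from the protocol article**
- Scale −3 to +3, a width of 6 points (Outcomes, Questionnaire).
- Expected return of 100% at t0 and t1 (Number of participants).
- α = 0.05, two-sided, unpaired (Statistical methods).
- 301 paramedics enabled to attend the courses (Study setting). Study participation is voluntary, so 301 is only an upper bound on N.

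**Assumptions (not in the document)**
- SD of 1 point at each time point.
- Return r at t2 from 50% to 100%.
- Gap G between the t2 means of responders and non-responders of 0.25, 0.5 or 1.0 points.

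**Shift of the t2 mean.** The full-group mean is r·m_R + (1 − r)·m_N. The responder mean exceeds it by

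(1 − r)(m_R − m_N) = (1 − r)G.

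With G = 0.5, this is 0.3 × 0.5 = 0.15 at 70% return and 0.5 × 0.5 = 0.25 at 50%.

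**Effect on the planned test.** SE = SD × √(1/301 + 1/(301r)). With no true change, the rejection rate is Φ(B/SE − 1.96) + Φ(−B/SE − 1.96), where B = (1 − r)G. At r = 0.7, SE = √(1/301 + 1/210.7) = 0.090, B/SE = 0.15/0.090 ≈ 1.67, and the rate is about 39%.

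**Worst-case width.** If nothing is assumed about non-responders, the full-group t2 mean can lie anywhere in a band of 6(1 − r).

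| Return at t2 | t2 forms (of 301) | Shift, G = 0.25 | Shift, G = 0.5 | Shift, G = 1.0 | SE | False-positive rate, G = 0.5 | Worst-case width |
|---|---|---|---|---|---|---|---|
| 100% | 301 | 0 | 0 | 0 | 0.082 | 5% | 0 |
| 90% | 271 | 0.025 | 0.05 | 0.10 | 0.084 | 9% | 0.6 |
| 80% | 241 | 0.05 | 0.10 | 0.20 | 0.086 | 21% | 1.2 |
| 70% | 211 | 0.075 | 0.15 | 0.30 | 0.090 | 39% | 1.8 |
| 50% | 150 | 0.125 | 0.25 | 0.50 | 0.100 | 71% | 3.0 |

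The false-positive rates are indicative only. They treat t0 and t2 as independent samples, as the planned test does, although the same people answer at both. A smaller N would give a larger SE and lower rates. The shift itself depends on neither N nor SD.

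**What matching removes.** Write G = G0 + C, where G0 is the gap already present at t0 and C is the gap in t0–t2 change. The unpaired comparison is off by (1 − r)(G0 + C); the change in matched responders is off by (1 − r)C. At 70% return and G = 0.5, a gap wholly present at t0 gives 0.15 unpaired and 0 matched. A gap wholly in change gives 0.15 in both. Matching therefore removes the part that t0 scores can show. The rest stays unobserved.

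**The case against.** The Discussion sentence is hedged. It expects results without special bias, follows a passage on the weaknesses of the video part, and sets no analysis rule. A reader might infer that the plan claims freedom from bias or would report t2 that way; the text does not go so far. What stands is that the sentence is not limited by time point and its stated reason has support only for t0 and t1.

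A reader might also infer that only t2 can answer the third hypothesis, since nobody has used the course in the field at t1. The documents do not say this. The hypothesis concerns subjective assessment and names no time point, and t1 repeats the questionnaire to check for change. A t0–t1 contrast can address it.

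The remark that the t2 survey runs alongside the video analysis may mean only the same period, which is compatible with web or email. It does not state paper forms or on-site collection. The consent sentence in Data management is too garbled to establish that t2 reaches only those who gave separate consent to contact. Both need clarifying; neither proves a restriction.

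The gap, the SD and the return rates are all assumed. That responders would be the more convinced participants is plausible but undocumented, so the direction of any shift is unknown.

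Finally, handling of missing data is commonly left to an analysis plan, and this is an article. That is fair, and its absence is not the point. The point is a positive statement in the text that the plan's own return figures do not carry to t2.

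**Conclusion.** The point holds in a limited form. No stated number is wrong, and the t0–t1 comparison is untouched if return there is as expected. The low-bias expectation does not extend to t2: no return is given, the route is described in three ways, non-response is not listed as a bias, and the unpaired test would set t2 responders against the fuller t0 group.

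Under an assumed 0.5-point gap, the t2 mean shifts by 0.15 points at 70% return and 0.25 at 50%. It does not shift at all if return is complete or responders and non-responders do not differ. These figures illustrate sensitivity; they do not predict the bias. What is at risk is the conclusion on durability and on self-rated application in practice after the course, for which t2 is needed.

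**What to change.** 1. In the Discussion, limit the low-bias expectation to t0 and t1, and add t2 non-response to the Bias section.
2. Use the four-digit code to compare t0 and t1 scores of t2 responders and non-responders. Report the t0–t2 change in matched responders beside that comparison, with the number returned at each time point.
3. State that t0–t1 addresses the third hypothesis as an immediate self-rated change, and that t0–t2 addresses durability and self-rated application in practice.
4. Reconcile Timepoint t2, Number of participants and Data collection methods into one t2 route, and record each participant's mode of response.

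Collection at the video sessions should not be required. The Bias section itself expects more motivated participants to come forward first for filming, so that route could bring in the same kind of selection.

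The cost is small: a few sentences and a little more analysis on records the plan already links by code. The t2 conclusion becomes more cautious, because any difference in change between responders and non-responders remains unobserved. If t2 has already been collected, steps 1 to 3 can still be done, and step 4 reduces to reporting the route and mode actually used.

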#### Video recording

In the 14 planned courses, 4 video recordings of scenarios completed by three-person teams will be made at t0. A total of 56 teams (168 participants) will be recorded. At t1, video recordings will be made. At this point, three records will be possible, and 12 teams per course will be filmed. In 14 courses, we expected up to 168 teams. The recordings will be made with four camcorders (Panasonic HD Camcorder HC-V100) and recorded on SD Memory Cards.

#### EMS operation protocols

Experts from the Department of Biometry of the University of Tuebingen Hospital (Tuebingen, Germany) recommended the evaluation of 400 protocols to detect changes of approximately 10% at a power of 0,8.

#### Data from the emergency department

pending

### Recruitment

The medical supervisor and the EMS agencies require the participants to attend the training. Study participation is voluntary.

### Data collection methods

#### Questionnaire

The questionnaires at t0 and t1 are distributed and collected during the courses. The survey at t2 (after one year) is conducted using the questionnaires in parallel with the video analysis.

#### Video recording

The videos are recorded at the beginning and end of the training and one year later.

#### EMS operation protocols

The EMS protocols are required in the context of the EMS field operations and archived in the EMS agencies in concordance with the local EMS regulations.

#### Data from the emergency department

pending.

### Data management

The data collection, coding, routing and analysis are coordinated with the data protection officer of the University of Tuebingen and the University of Tuebingen Hospital. The participants will be informed about the study prior to the course, and their questions about it will be answered.

The declarations of consent from the participants for the video analysis are available; the consent declarations assure permission for the recording, analysis and storage of the study data. The number of participants will be registered as a negative figure.

For the questionnaires and time contact, t2 is a declaration of consent for the available participants. This declaration is separated from the questionnaires on site. The questionnaires are pseudonymized with a four-digit code to represent the relationship between the different times, not to establish a connection to the participants.

The analysis of the defined characteristics in the EMS-operation protocols is unrelated to the patient data (including the last name, first name and date of birth). Hessian EMS law § 17 permits the use of evaluation data in the context of quality assurance.

### Statistical methods

The statistical analysis of the end points of the video is based on the assessment tool. The achievable sum scores from the assessment tool are combined with the respective measuring points and, depending on the scale levels, as the mean or median and compared as the independent samples. The statistical tests are dependent on the scale level, and the results are given with the confidence intervals.

The statistical analysis of the questionnaires used the three time points t0, t1 and t2. The individual questionnaires at the respective time points are recorded using Microsoft Excel® 2010 (Redmond, USA). The data are matched in IBM SPSS Statistics 21 software (Illinois, USA) with the pseudonymous ID codes. The data are normally distributed and considered to be metric; the statistical calculation was performed using Student’s t-test for the unpaired two-sided sampling. The significance level is set at α = 0.05.

The evaluations of the EMS protocols in terms of three items, allergies, medication, and the patient’s medical history are conducted by counting the frequency before and after the comparison. The significance level is set at α = 0.1.

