## Methods

### Study setting

The study is performed in the EMS of the city of Wiesbaden and Rhein-Taunus-Kreis (Germany). The operational area in Wiesbaden has five commissioned EMS agencies (four charities, one private provider). The EMS in Wiesbaden has 375 paramedics and serves 462 098 inhabitants.

With regard to the training, close cooperation occurs with the neighboring Rheingau-Taunus-Kreis area. In the context of various difficulties and problems, the controlling authority enabled 301 paramedics from both EMS services to attend the PHTLS courses to create uniform structures and principles [28].

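### Video scores at t0 and t1 come from the same 14 courses but are compared as independent samples, so the standard error does not match the design

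*Protocol article*

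**What the plan says.** Statistical methods states that video sum scores are summarised at each measuring point "as the mean or median and compared as the independent samples". It adds: "The statistical tests are dependent on the scale level, and the results are given with the confidence intervals". It names no pairing and no course or team term for the videos, and it gives no significance level for them.

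The layout is under Number of participants, Video recording. For t0: "In the 14 planned courses, 4 video recordings of scenarios completed by three-person teams will be made at t0", then "A total of 56 teams (168 participants) will be recorded". For t1: "three records will be possible, and 12 teams per course will be filmed", with up to 168 teams expected over the 14 courses. Timepoint t1 says that at the end of the course "the participants’ survey with the questionnaire and the video recording are repeated to verify the changes". Study setting says that the authority "enabled 301 paramedics from both EMS services to attend the PHTLS courses".

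**The concern.** An independent-samples comparison assumes that every t0 score is unrelated to every t1 score and that scores within a time point are unrelated to each other. Here both sets come from the same 14 courses, each with its own trainees and course conditions, filmed before and after training. The trial has a single arm, so the video contrast is before-after within one cohort.

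This contrast bears on the hypothesis of structured, priority-based care in scenarios, one of three hypotheses that the protocol lists without ranking. If the standard error does not fit, the p-value and the promised confidence interval for the change may be too cautious or too optimistic, and the reader cannot tell which.

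**Working it through.** **1. The plan's counts.** 14 × 4 = 56 teams at t0; 56 × 3 = 168 participants; 14 × 12 = 168 teams at t1. All three stated figures reproduce.

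**2. Places at t1.** If t1 teams also have three members, 168 × 3 = 504 places, or 36 per course. Against 301 trainees this is 504/301 = 1.67 places each. If all 301 attend these 14 courses, a course has 301/14 = 21.5 people. Even two-person teams would need 168 × 2 = 336 places, more than 301. At the full 168 teams, then, some people would appear more than once at t1. The t1 team size and the spread of trainees over courses are assumptions.

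**3. Independent-samples standard error.** With team-score variance set to 1: √(1/56 + 1/168) = √0.02381 = 0.154.

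**4. Standard error under course effects.** Let v_c be the share of variance from stable course differences and v_ct the share from course differences specific to a time point. Leaving shared persons aside,

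Var(t1 − t0) = 2·v_ct/14 + (1 − v_c − v_ct)·(1/56 + 1/168).

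- v_c = 0.2, v_ct = 0: √(0.8 × 0.02381) = 0.138. The independent-samples value is 0.154/0.138 = 1.12 times too large.
- v_c = 0, v_ct = 0.1: √(0.01429 + 0.02143) = 0.189. The independent-samples value is 0.154/0.189 = 0.82 of what it should be.
- Break-even: 0.1429·v_ct = 0.0238·(v_c + v_ct), so v_ct = v_c/5. Below that the test is conservative, above it anti-conservative. Shared persons move the break-even point upward.

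**5. Simulated rejection rates.** Settings: 14 courses, 4 and 12 three-person teams, 21 people per course, person share 0.25, no true change, two-sided t-test at 5%. All shares are assumed, as are the t-test and the 5% level.

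| Stable course share | Course-by-time share | Independent test rejects |
|---|---|---|
| 0 | 0 (shared persons only) | about 4% |
| 0.20 | 0 | about 1.5% |
| 0.10 | 0.05 | 5.3% |
| 0.20 | 0.05 | 4.8% |
| 0.20 | 0.10 | 8.0% |
| 0.20 | 0.20 | 13.9% |
| 0 | 0.10 | about 9% |
| 0 | 0.20 | about 15 to 16% |

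A paired t-test on the 14 course-mean differences stays at about 4 to 6%. For a true change of 0.4 SD with a stable course share of 0.2, its power is about 0.85, against 0.78 for the independent test. Separate runs gave 0.82 to 0.87 for the paired test, so the gain depends on the assumptions.

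**6. Repeat members.** The first table row shows that repeat appearances and t0–t1 overlap alone do not inflate the test of change. They do affect an interval for the t1 mean taken alone. With course shares of 0 to 0.2 and person shares of 0.2 to 0.5, the independent standard error of that mean is about 0.077, against a true 0.081 to 0.158.

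**The case against.** The strongest reply is that much of the dependence is inferred. The 168 teams at t1 are a ceiling, the t1 team size is not restated, and Study setting says only that 301 people were enabled to attend. The Participants paragraph under Bias speaks conditionally of the same people being filmed twice, and discusses this as a matter of representativeness. All of this stands, so the degree of person overlap must be treated as an assumption. It does not rescue the stated rule, because recordings from the same 14 courses before and after training are grouped by course even if no person is filmed twice.

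A reader might infer that the planned test produces too many false positives, or that repeated team members at t1 cause this. The document supports neither. With shared course and person effects only, the test is conservative. Inflation needs course-by-time variation, for which no figure is given, and modest amounts of both kinds of course effect roughly cancel.

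A reader might also say that an article leaves such detail to an analysis plan. That would answer an omission, but here the article itself states the independent-samples rule.

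**Conclusion.** The point holds as a mismatch between a stated analysis and the stated design. Its firm basis is the 14 courses common to both time points; repeat appearances are likely but not established. Its size cannot be fixed from the document: across the assumed shares, the nominal 5% test runs from about 1.5% through nominal to about 16%. The low end costs power, and the high end overstates the evidence. Because the direction is unknown and some plausible settings are close to nominal, this is something that should be fixed, not a flaw that invalidates the video component. The conclusion covers the t0–t1 contrast only; the document gives no team count or course structure for the videos at t2.

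**What to change.** In Statistical methods, replace the independent-samples wording for the t0–t1 video contrast with a within-course analysis, in one of two forms:

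- For each course, take the mean t1 score minus the mean t0 score. Analyse the 14 differences with a paired t-test and its confidence interval. This takes in all dependence within a course, including repeat members, provided nobody attends two courses.
- Or fit a linear mixed model to the sum score, with time point fixed and random course and course-by-time effects.

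Only the course label of each video is needed. The four-digit questionnaire codes should not be attached to the recordings, because Data management says that they are not meant to link back to participants; a term for individual team membership is therefore not proposed. Nor is a run-order covariate: the Discussion describes t1 as differing from t0, "with the difference being that in t1, the cases are sequential instead of parallel", so run order exists at only one time point and would be entangled with the time effect.

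The cost is a sentence of analysis text and a course identifier per recording. The course-level test has 14 − 1 = 13 degrees of freedom, and its interval will be wider if courses differ in how much they change.

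### The questionnaires are matched person by person across t0, t1 and t2 but then tested with an unpaired t-test; the error is conservative and costs precision

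*Protocol article*

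**What the plan says.** The Timepoint sections survey the same people repeatedly: before the course (t0), at its end (t1), and at t2, where "After one year, the participants of the course will be interviewed again with the questionnaire". Under Data management, "The questionnaires are pseudonymized with a four-digit code to represent the relationship between the different times". That section gives the code no other use.

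Under Statistical methods, "The statistical analysis of the questionnaires used the three time points t0, t1 and t2", and "The data are matched in IBM SPSS Statistics 21 software (Illinois, USA) with the pseudonymous ID codes". The article then declares the data normal and metric and names the test: "the statistical calculation was performed using Student’s t-test for the unpaired two-sided sampling", at a two-sided level of 0.05. This is the only test named for the questionnaire, which carries the third hypothesis (that participants feel better and safer in applying the principles).

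Three further statements bear on the point:
- The Trial design section describes a single-arm, uncontrolled study.
- Under Outcomes, Questionnaire: "A steady (metric) scale to ± 3 (positive/negative), including zero is used".
- Under Number of participants, Questionnaire, full return is expected at t0 and t1, while for the last round "The questionnaire at time t2 will be web-based or distributed via email".

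No section names a paired test or a repeated-measures model for the questionnaire, or gives a reason for setting the pairing aside.

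**The concern.** Matching has no function in an unpaired comparison of time points. The article builds a linkage, carries it out, and then names a test that does not use it. With a single arm there is no between-group contrast that an unpaired test could serve; the only question is how each person changes.

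This is not a detail left for an analysis plan. A specific test is stated, and its independence assumption is broken by the design described in the same article. An analyst who followed the sentence would report wrong standard errors, confidence intervals and p-values for one of the three hypotheses.

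**Working it through.** There is no figure of the plan's own to reproduce: the article gives no power, effect size, standard deviation or correlation for the questionnaire.

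**Inputs from the article.** Two-sided alpha 0.05; the same participants at each time point; up to 301 people attending courses (Study setting). That number is an upper bound, because study participation is voluntary (Recruitment).

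**Assumptions.** Equal standard deviation at both time points, set to 1; n complete pairs; within-person correlation rho of 0.3, 0.5 or 0.7.

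**Standard errors of the mean change**
- Used by the unpaired test: SE_u = sqrt(2/n).
- Correct for pairs: SE_p = sqrt(2(1 − rho)/n).
- Ratio: R = SE_u/SE_p = 1/sqrt(1 − rho), whatever n is.

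**Type I error.** The unpaired test rejects when the observed change exceeds 1.96 × SE_u in size. The change really varies with SE_p, so the true level is 2(1 − Phi(1.96 R)).

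**Power.** Take a true change that gives the paired test 80% power, that is 1.960 + 0.8416 = 2.8016 times SE_p. The unpaired test detects it with probability Phi((2.8016 SE_p − 1.96 SE_u)/SE_p) = Phi(2.8016 − 1.96 R).

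| rho | R | 1.96 R | True type I error | 2.8016 − 1.96 R | Unpaired power | Sample-size factor 1/(1 − rho) |
|---|---|---|---|---|---|---|
| 0.3 | 1.20 | 2.343 | 0.019 | 0.459 | 68% | 1.43 |
| 0.5 | 1.41 | 2.772 | 0.006 | 0.030 | 51% | 2.00 |
| 0.7 | 1.83 | 3.578 | 0.0003 | −0.777 | 22% | 3.33 |

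At rho = 0 the two tests agree.

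**Check at the upper-bound sample size.** With n = 301 and an assumed true change of 0.2 SD, power (unpaired against paired) is 72.2% against 83.5% at rho 0.3, 75.7% against 93.4% at rho 0.5, and 81.6% against 99.4% at rho 0.7. A simulation of 10,000 runs gave 75.5% against 93.2% at rho 0.5 and 80.9% against 99.4% at rho 0.7. With no true change, the unpaired test rejected in 0.46% and 0.02% of runs at these two correlations, and the paired test in 4.7% and 5.4%.

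**Direction.** Conservatism depends on rho being positive, as is usual for repeated answers by one person. At an illustrative rho of −0.3 the unpaired test would have a type I error of 0.086.

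**The case against.** The strongest reply is that little harm follows. With positive correlation the unpaired test cannot manufacture a training benefit; it only makes one harder to show. Nothing in the study is powered on the questionnaire, so the 80% starting point is illustrative. If participation comes near 301, the independence formula already gives a detectable change of 2.8016 × sqrt(2/301) = 0.228 SD at 80% power, and a large gain from t0 to t1 would be significant with either test. All of this stands. It limits the consequence but does not make the named test suitable for matched data. If the word unpaired is only a slip, the sentence still needs correcting.

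Four stronger readings are tempting, and the article does not support them.

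- **That the loss is worst for the one-year contrast.** The inflation grows with rho. The article gives no correlation for either contrast, and nothing suggests a higher one over a year than across a two-day course. If some t2 forms are missing and all t0 forms are used, the samples only partly overlap and the factor 1/sqrt(1 − rho) no longer applies exactly.
- **That everyone at t0 is compared with a self-selected group at t2.** Web or email return makes non-response possible. But the article says the records are matched before testing and does not say which of them enter the test. Its Discussion also expects a very high response rate.
- **That the normality statement invalidates the analysis.** A bounded scale may produce skewed scores after a course, but no data are shown, and at sample sizes near 301 a t-test on means tolerates this. The wording is poor; the effect is minor.
- **That the power loss can be found by dividing 2.8016 by R and subtracting 1.96.** This gives 65%, 51% and 34%. It is wrong, because the unpaired statistic has standard deviation 1/R here, not 1.

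**Conclusion.** The point holds. The article pairs the questionnaires and then names a test for independent samples, without a reason. For complete pairs with rho between 0.3 and 0.7, standard errors are 20% to 83% too large. The test runs at a true level between about 0.019 and 0.0003, and 80% paired power falls to between about 68% and 22%. These figures rest on assumed correlations, equal variances and complete pairs. The last is close to what the article expects for t0 and t1 and is less certain for t2.

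A reader might infer that a positive questionnaire result would be untrustworthy. That does not follow: with positive correlation, significance reached by the unpaired test is reached against a stricter standard than intended. What is at risk is a real but modest change that goes undetected, and intervals that understate the precision of the data. It is a clear error with limited harm to conclusions and a very cheap remedy, so it should be corrected.

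**What to change.** In Statistical methods, replace the unpaired test with one of these:

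1. Paired t-tests on the matched codes for t1 minus t0 and t2 minus t0, each with a 95% confidence interval. This is enough to cure the defect. It uses only people with both forms, so the t2 contrast describes those who returned the t2 questionnaire.
2. One repeated-measures mixed model over t0, t1 and t2, with time as a fixed effect and the within-participant correlation modelled, reporting the same two contrasts with 95% confidence intervals. This keeps participants without a t2 return through their t0 and t1 answers.

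Replace the assertion of normality with a statement that the paired changes are analysed as approximately normal (minor).

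The cost is one paragraph. The code is already planned and the matching step is already described, so no new data, consent or software is needed.
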